### 2.7. Sample Size

Based on the results of Schuck and colleagues (2014) [14], our power calculation (Stata 12.1, StataCorp., College Station, TX, USA) indicated that 72 parents per implementation approach (36 intervention and 36 control) is sufficient to detect 7-day prevalence abstinence at three months post-intervention with a large effect (*p*_1_ = 0.445, *p*_2_ = 0.121, Power = 0.80, α = 0.05). Because we want to examine differences in smoking cessation rates between the two implementation approaches, we have to double from 72 to 144 parents. Based on the drop-out rates at 3-month follow-up of Schuck et al., 2014 [14] (i.e., 10% in the control group and 3.9% in the intervention group), we will anticipate 10% drop-out. This means that we will aim to recruit a minimum of 158 participating parents in total.

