The existing research suggests that most parents want to quit smoking and even tried to quit smoking [10]. In addition, most parents would accept smoking cessation support, such as telephone counseling [11]. A review consisting of 77 (quasi) randomized controlled trials (RCT) on telephone counseling confirmed that telephone counseling is effective in increasing smoking cessation rates [12]. Moreover, Hollis et al., 2007 [13] found that telephone counseling is cost-effective (i.e., the degree to which something is effective in relation to its costs). Recently, a tailored telephone counseling program for smoking parents was tested in The Netherlands [14]. Parents who smoke (*N* = 512) were recruited in an RCT and assigned to the intervention condition (i.e., tailored telephone counseling and supplementary materials) or the control condition (i.e., a standard self-help brochure). Parents who received telephone counseling were more likely to report 7-day point prevalence abstinence at three months post-intervention (44.5% versus 12.1%; OR = 6.89, 95% CI = 4.18–11.36) and to use nicotine replacement therapy (48.4% versus 20.9%) compared to parents who received a standard self-help brochure. Among parents who did not quit smoking, those who received telephone counseling were more likely to make a quit attempt (85.2% versus 68.1%) and to implement a complete home smoking ban (39.5% versus 26.1%) compared to parents who received the self-help brochure. Altogether, this study provided evidence that telephone counseling tailored to smoking parents is effective in helping parents quit smoking and developing parenting practices that protect their offspring from ETS exposure [14].

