
### 2.10. Statistical Analyses

Statistical analyses will be carried out to assess whether the randomization results in an equal baseline distribution of relevant participant characteristics across conditions. In case of group differences at baseline, confounding variables will be included in subsequent analyses. All analyses will be conducted in accordance with the intention-to-treat principle (i.e., all parents randomized to one of the two conditions will be included in the analyses examining the study hypotheses) as per the Consolidated Standards of Reporting Trials [53]. Moreover, a completers-only analyses will be conducted, i.e., only parents with outcome data on all assessments will be included in the analyses. To compare cessation rates across different groups, logistic regression analyses will be conducted. In addition, Mplus will be used to test for moderation and subsequently, multi-group testing with bootstrapping will be conducted to assess differences between recruitment approaches. Effect sizes and 95% confidence intervals (CI) will be reported to determine the magnitude and effect of the intervention.

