## 4. Conclusions

The results of this study will reveal whether the telephone counseling is effective in “real life” conditions. If the counseling will not be as strong as we expect we will search for reasons and try to clarify why our results do not correspond to the results of Schuck et al., 2014 [14]. Consequently, we will think about how the telephone counseling can be improved. The results of Hayes et al., 2017 [57] could be important and relevant suggestions for the improvement of the telephone counseling. This study will also provide information on how and where to implement the telephone counseling for smoking parents in the most optimal manner in The Netherlands. If all four implementation channels will turn out successful in recruiting smoking parents (i.e., high recruitment rates and similar costs/participant), we will be able to conclude that a combination of all four implementation channels should be used to implement the telephone counseling. In contrast, if only one implementation channel turns out to be unsuccessful (i.e., extremely low recruitment rates and/or low quit rates), this particular channel should not be used to implement this program.

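### Doubling the sample from 72 to 144 sizes an intervention-control test in each approach; it does not give 80% power for the between-approach comparison offered as its reason

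*Protocol article*

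**What the plan says.** Section 2.7 takes the quit rates of the earlier Dutch efficacy trial, which the Introduction reports as "44.5% versus 12.1%; OR = 6.89, 95% CI = 4.18–11.36". With 80% power and α = 0.05 it reaches this conclusion: "72 parents per implementation approach (36 intervention and 36 control) is sufficient to detect 7-day prevalence abstinence at three months post-intervention with a large effect". The next step is the doubling: "Because we want to examine differences in smoking cessation rates between the two implementation approaches, we have to double from 72 to 144 parents". A 10% drop-out allowance then brings the target to 158. The section names no between-approach difference, no interaction effect and no power for either.

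The between-approach question is a stated aim. The last paragraph of the Introduction asks whether the counselling's effect varies with the approach. Section 2.10 plans a moderation test in Mplus, after which "multi-group testing with bootstrapping will be conducted to assess differences between recruitment approaches". Section 4 adds that a channel which proves unsuccessful, described as "extremely low recruitment rates and/or low quit rates", should not be used.

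**The concern.** The reason given for 144 and the calculation behind it address different questions. A test of 36 v 36 asks whether counselling beats the brochure inside one approach. Running it twice gives two such tests. Whether the two effects differ is a contrast of four cells. Its variance is the sum of both within-approach variances, so it needs far more parents for a difference of the same size.

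Two readings are at stake. A non-significant moderation test could be taken to mean that counselling works equally well through either approach, when the trial had little chance of showing otherwise. And a channel could be set aside for a low observed quit rate that reflects chance or the kind of parent it attracts.

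**Working it through.** **Inputs.** From 2.7: p1 = 0.445, p2 = 0.121, 36 per arm per approach, α = 0.05 (taken as two-sided), power 0.80. Assumptions of this check: an equal split between approaches, 36 evaluable per cell, and the quit rates of the second approach as listed below.

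**1. The plan's own figure.** With mean rate 0.283, the usual two-proportion formula gives

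n = [1.960·√(2·0.283·0.717) + 0.842·√(0.445·0.555 + 0.121·0.879)]² / 0.324² = 29.1, so 30 per arm.

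The continuity correction, n/4·[1 + √(1 + 4/(n·0.324))]², gives 35.04, so 36. The 36 is therefore reproduced as a continuity-corrected intervention-control test within one approach. Then 36 + 36 = 72, doubled to 144, and 144 × 1.10 = 158.4, consistent with the stated 158. None of this arithmetic is wrong.

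**2. What 144 does support.** Within one approach (36 v 36), power is at least 80% by the corrected calculation and 88% without correction. Pooled over approaches (72 v 72), power is 99% at the planning effect.

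**3. Interaction, effect absent in one approach.** On the odds-ratio scale the contrast is the difference in log odds ratios, with variance equal to the sum of 1/(36·p·(1−p)) over the four cells. With 44.5% v 12.1% in one approach and 12.1% in both arms of the other:

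- difference = logit(0.445) − logit(0.121) = 1.762
- variance = 0.1125 + 3 × 0.2612 = 0.896, so SE = 0.947
- z = 1.762/0.947 = 1.86, power 46% (simulation: Wald 44%, likelihood ratio 46%)

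On the risk-difference scale the difference is 0.324, the SE is √(Σ p(1−p)/36) = 0.125, and power is 73%.

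The result depends on the quit rate where counselling has no effect:

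| Common quit rate, no-effect approach | Power, odds ratio | Power, risk difference |
|---|---|---|
| 12.1% | 46% | 73% |
| 20% | 55% | 66% |
| 28.3% | 59% | 61% |
| 44.5% | 62% | 56% |

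For 80% power on the odds-ratio scale, the first row needs about 82 per cell (about 328 analysed) and the last about 55 per cell (about 220).

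**4. Interaction, effect half as large in one approach (control 12.1%).** Halving the risk difference (28.3% v 12.1%) gives power of 13% (odds ratio) and 22% (risk difference). Halving the log odds ratio (24.9% v 12.1%) gives 17% and 31%.

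**5. Read as overall cessation, 72 v 72.** Around 28.3%, SE = √(2·0.283·0.717/72) = 0.075. The gap detectable with 80% power is 2.80 × 0.075 = 0.21, about 21 points.

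**6. Channels.** If the four channels recruited equally, each would hold 144/4 = 36 to 158/4 = 39.5 parents over both arms. The plan sets no such quota.

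**The case against.** The power of 0.80 in 2.7 is attached to the 72 parents per approach. The doubling sentence speaks only of examining differences and claims no power for an interaction. Wanting an adequately sized comparison in each approach is a coherent reason to double, and all the stated numbers follow. The hypothesis of counselling versus brochure is stated in the Abstract, Introduction and Discussion, and it is well powered. Section 2.10 already promises effect sizes with 95% confidence intervals. The remark on channels in section 4 is discussion, not a formal decision rule.

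Most of this stands, and it limits the point to a mismatch of rationale. It does not remove the mismatch: the sentence gives the between-approach comparison as the reason for 144, that comparison is an aim with a planned test, and the calculation does not size it.

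A reader might infer stronger claims that the document does not support:

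- That interaction power is at most 46%. This is one scenario; others with no effect in one approach reach 62% on the odds-ratio scale at the planning rates. With the reported odds ratio of 6.89 the figures are 53–70%, and a full reversal of effect would be detected with about 98% power.
- That the two within-approach tests are both significant with only 0.8 × 0.8 = 64% probability. This uses the continuity-corrected power, whereas 2.10 plans logistic regression, which applies no such correction. At 88% each the product is about 77%.
- That the pooled comparison is missing. Only its power figure is unstated.

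**Conclusion.** The point holds as a mismatch between the stated reason for the sample size and what the calculation covers. The 144 parents support the pooled arm comparison and an arm comparison within each approach. They do not give 80% power for the difference between approaches in any scenario checked without a reversal of effect: 46–73% over both scales when the planned effect is wholly lost in one approach, and 13–31% when it is halved.

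These figures assume the planning rates, 36 evaluable parents in every cell and an equal split between approaches. An unequal split would generally lower them. A true effect in one approach well above the planning value would raise them. The primary conclusion of the trial is not affected. What is affected is how the moderation result, and quit rates by channel, may be read.

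**What to change.** Reword 2.7 to say that 144 evaluable parents give about 99% power for the pooled arm comparison at the planning effect and at least 80% within each approach (80% continuity-corrected, about 88% uncorrected). It should add that, at the planning effect, the between-approach comparison does not reach 80% power unless the effect reverses.

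In 2.10, label the moderation and multi-group results exploratory. Report the difference between the approach-specific effects with its 95% CI, and state that a non-significant moderation test will not be read as equal effectiveness.

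In section 4, do not let an observed low quit rate by itself rule out a channel: parents are not randomised to channels, and each will contribute few of them (about 36–40 if recruitment is equal, which is an assumption).

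The cost is wording only. No parents are added and no analysis is lost. If a confirmatory between-approach test is wanted instead, the trial must be sized for a stated interaction, which on the odds-ratio scale means about 220–328 analysed parents even for complete loss of the effect in one approach.

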In sum, this effectiveness study takes a novel method by examining the recruitment success of two implementation approaches (i.e., a mass media approach and a health care approach) to test the (cost)effectiveness of a telephone smoking cessation counseling and whether the effectiveness depends on the implementation approach. The mass media approach includes two implementation channels: mass mailings through primary schools and online mass media. The health care approach also consists of two implementation channels: general health care and youth health care. A 2-arm RCT will be carried out to test the (cost)effectiveness of the telephone counseling. Based on earlier results of Schuck et al., 2014 [14], it is expected that parents who receive telephone counseling show higher smoking cessation rates at 3-month post-intervention compared to parents who receive the control condition. Concerning the implementation of the telephone counseling, a process evaluation of the recruitment success will be conducted for two implementation approaches. It is expected that (youth) health care will be a more promising implementation approach for connecting smoking parents with the telephone counseling compared to mass media channels (online approach and mass mailings trough primary schools), as most of these parents are motivated to quit and find it acceptable to be directed to telephone counseling in the context of their child’s health [11,34].

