### 2.2. Participants and Recruitment

In total, 158 smoking parents will be recruited through four different implementation channels (i.e., primary schools, online mass media, health care, and youth health care), which will be distinguished as two different implementation approaches (mass media approach and health care approach).

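### Section 2.7 claims 80% power per approach but sets only a total target, so the claim holds only if recruitment is roughly equal; the drop-out allowance is also two parents short (158, not 160)

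*Protocol article*

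**What the plan says.** Section 2.7 of the protocol article takes its abstinence rates from the earlier Dutch efficacy trial (0.445 with counseling, 0.121 with the brochure), with "Power = 0.80, α = 0.05". From these it concludes that "72 parents per implementation approach (36 intervention and 36 control) is sufficient". Because differences between the two approaches are to be examined, "we have to double from 72 to 144 parents". It quotes the earlier trial's drop-out (10% control, 3.9% intervention), adopts 10%, and ends: "This means that we will aim to recruit a minimum of 158 participating parents in total".

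The figure 158 also appears in the Abstract and in sections 2.1 and 2.2. Section 2.2 reads: "In total, 158 smoking parents will be recruited through four different implementation channels". No section gives a minimum, cap or quota for an approach or channel. Section 2.6 stratifies randomization by channel, which balances the arms within a channel but does not fix how many parents each channel contributes.

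The Introduction states: "It is expected that (youth) health care will be a more promising implementation approach". Section 2.10 plans logistic regression on all randomized parents, a completers-only analysis, and a moderation analysis with multi-group testing for differences between approaches.

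**The concern.** The sample-size argument starts at one level and ends at another. The 80% is worked out inside a single approach, and the sample is doubled so that both approaches can be examined. The recruitment target then drops the per-approach condition and becomes one total across four channels. That total can be reached while one approach falls well short of 72, and the stated power for that approach is then lost without any departure from the plan.

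The total also misses its own requirement slightly: it adds 10% to the evaluable number when it should divide by the 90% expected to remain.

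At stake is how the by-approach results will be read. A non-significant intervention effect in the smaller approach could be taken as evidence that counseling does not work there, when the comparison had much less than the advertised power. Section 4 would drop a channel for low quit rates, so such readings could carry weight.

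**Working it through.** **Inputs.** From section 2.7: p1 = 0.445, p2 = 0.121, power 0.80, α = 0.05, 36 per arm, 144 in total, 10% drop-out, target 158. Two-sided testing is an assumption, since the article does not state it; it is supported by the first step.

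**1. Reproduce 36 per arm.** Difference d = 0.324; mean rate 0.283; √(2 × 0.283 × 0.717) = 0.6370; √(0.445 × 0.555 + 0.121 × 0.879) = 0.5944.

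- Without continuity correction: n = (1.960 × 0.6370 + 0.8416 × 0.5944)² / 0.324² = 29.1, so 30 per arm.
- With correction: (29.135/4) × [1 + √(1 + 4/(29.135 × 0.324))]² = 35.04, so 36 per arm.

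The two-sided corrected version gives the plan's 36. One-sided versions give 29 (corrected) and 23 (uncorrected).

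**2. Drop-out.**

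- 144 × 1.10 = 158.4, rounded down to 158.
- 158 × 0.90 = 142.2, below 144.
- 144 / 0.90 = 160, that is 72 / 0.90 = 80 per approach and 40 per arm within each.
- With the arm-specific rates quoted in 2.7: 72/0.90 + 72/0.961 = 80 + 74.9 = 154.9, which 158 would cover.

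**3. Power in the smaller approach.** With n evaluable per arm, power = Φ{[d − c − 1.960 × 0.6370/√n] / (0.5944/√n)}, where c = 1/n with continuity correction and 0 without. Here n = 158 × share × 0.90 / 2. The splits are illustrative.

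| Split | Recruited in smaller approach | n per arm | Power, corrected | Power, uncorrected |
|---|---|---|---|---|
| 50:50 | 79 | 35.6 | 80.7% | 87.5% |
| 60:40 | 63 | 28.4 | 69% | 79% |
| 70:30 | 47 | 21.3 | 52% | 66% |
| 80:20 | 32 | 14.2 | 31% | 48% |

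For 60:40, corrected: (0.324 − 0.0352 − 0.2341)/0.1115 = 0.49, and Φ(0.49) = 0.69.

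**4. Pooled comparison.** With about 71 evaluable per arm over both approaches and the same rates in each, power is about 99% by either version, whatever the split.

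**5. Differences between approaches.** Take exactly 36 per cell, the full effect in one approach and none in the other (both arms at 0.121).

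- Difference in log odds ratios: ln(0.445/0.555) − ln(0.121/0.879) = 1.762.
- Variance: 1/(36 × 0.445 × 0.555) + 3/(36 × 0.121 × 0.879) = 0.1125 + 0.7835 = 0.896, so the standard error is 0.947.
- Power: Φ(1.762/0.947 − 1.960) = Φ(−0.10), about 46%.

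If both arms of the approach without effect were instead at 0.445, the variance is 3 × 0.1125 + 0.2612 = 0.599, the standard error 0.774, and power Φ(0.32), about 62%. Both are below 80%.

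**The case against.** Much of the case on the other side stands.

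- **The inflation slip has no practical consequence.** With an even split, 158 still gives 80.7% by the plan's apparent method. The flat 10% is conservative against the quoted 3.9% in the intervention arm, 158 is called a minimum, and the intention-to-treat analysis includes all randomized parents. A reader might infer that the trial is underpowered because it does not recruit 160; the figures do not support that.
- **72 is described as sufficient, not as necessary.** It is the minimum only with continuity correction; without it, 60 per approach (30 per arm) would do. That softens the loss at 60:40 (79%) but not at 70:30 (66%).
- **The article does not predict an uneven trial sample.** A reader might infer from the Introduction that it does. It expects health care to be the more promising approach, and section 2.11 defines recruitment success as a ratio of sign-ups to intervention starts. Neither is an enrolment split, and recruitment effort could be adjusted over the two years. What remains is that equal numbers are assumed and nothing in the text secures them.
- **The primary hypothesis is untouched.** It compares counseling with the brochure overall.

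One could add that quotas are operational detail for the full protocol. Their absence is not the point. The point is that the power statement printed in section 2.7 depends on a condition that the printed target does not carry.

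**Conclusion.** The point holds in a limited form. The target of 158 is wrong by two parents under the plan's own 10% drop-out, which is immaterial alone. The more important defect is that the 80% in section 2.7 is true per approach only if recruitment is roughly equal, while only a total is fixed. If the split were 60:40 or 70:30, power in the smaller approach would be 69% or 52% with continuity correction (79% or 66% without). These splits are assumptions, and the rates are those of the efficacy trial.

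The pooled primary comparison is not threatened, at about 99% under the same rates. Equally, an even split would not rescue the aim for which the sample was doubled. The 80% concerns counseling against brochure within an approach, and the test of differences between approaches has about 46% power at 36 per cell even when one approach has the full effect and the other none (both arms at 0.121). It would be a mistake to read 80 per approach as powering that test.

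**What to change.** 1. Replace 158 by 160, stated as 80 per approach (40 per arm within each), in the Abstract and in sections 2.1, 2.2 and 2.7.
2. In 2.7, state that the 80% refers to the intervention-control comparison within an approach, and only if that approach reaches about 72 evaluable parents.
3. Add that otherwise the pooled comparison is the confirmatory one (about 99% power at the assumed rates) and within-approach results are exploratory.
4. Add that the 80% does not cover the moderation test between approaches, and give its power with the scenario assumed.

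The cost is two more parents, some wording and a less favourable power statement. Holding out for 80 in the slower approach might lengthen recruitment; if that is not feasible, items 2 to 4 alone make the statement accurate.

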### 2.8. Outcomes

The primary outcome measure will be 7-day point prevalence abstinence at three months post-intervention. In addition, secondary outcome measures include: (1) occurrence of at least 24 h of abstinence at three months post-intervention; (2) increase in motivation to quit; (3) number and duration of quit attempts; (4) use of and adherence to nicotine replacement therapy; (5) implementation of smoking restrictions at home; and (6) change in smoking-related cognitions (e.g., social norms, attitudes towards smoking, and self-efficacy). Moreover, to compare the success rates in this study with other studies, one outcome of the Russell Standard (Clinical) version 2 [47] will also be included as a secondary outcome (i.e., 14-day point prevalence abstinence at 4 weeks after the designed quit date).

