## 2. Materials and Methods

### 2.1. Study Design

Because both the (cost)effectiveness and the implementation strategy of the telephone counseling will be examined, an effectiveness-implementation hybrid design will be adopted. This design has multiple advantages, including improving the capability to identify important implementation strategies and interactions, increasing the speed of implementing the interventions once deemed effective, and providing valuable information for decision makers [41,42]. With respect to the RCT, parents who smoke will receive two online questionnaires during a period of three months. In total, 158 smoking parents will be randomly assigned to the intervention (i.e., telephone counseling) or control (i.e., self-help brochure) condition. The study design is depicted in Figure 1.

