#### 2.4.1. Telephone Counseling Condition

In the telephone counseling condition, parents will receive up to six proactive counseling phone calls (20 min) over a period of 10 weeks. The telephone counseling is based on Motivational Interviewing (MI), which is “a directive, client-centered counseling style for eliciting behavior change by helping clients to explore and resolve ambivalence” [43]. It aims to motivate patients to change, to focus on the changes that are most important to them, and to focus on their strengths instead of weaknesses and problems [44]. MI has been widely used for smoking cessation programs, and it has proven effective for smoking cessation support [45,46].

The telephone counseling will be performed by professional smoking cessation counselors of SineFuma who are thoroughly trained, experienced, and certified in delivering telephone counseling to support smoking cessation. During the six calls, multiple topics will be discussed, including information about nicotine replacement therapy, personal motivation and smoking history, preparation for the quit date, withdrawal symptoms, craving, relapse prevention, weight gain, and having a smoke-free future. Since the smoking cessation coaches will book individual appointment with parents at times that suit them, uptake will be maximized and drop-outs will be minimized. The results of Schuck et al., 2014 [14] showed that in the telephone counseling condition 224 parents (87.5%) indicated receiving at least one counseling call and 212 (82.8%) indicated receiving at least three calls. Of parents who received calls, the mean number of calls received was 5.5 (SD = 1.8). In addition, all parents will receive a supplementary brochure on smoking cessation, which was designed for this study as supplementary material for parents. The brochure (Rookvrije Ouders (Smoke-free Parents)) consists of 22 pages (color-printed, size: 30 × 21 centimeters) and provides didactic information about smoking that is relevant to parents (e.g., information about ETS) as well as exercises, motivational messages, and tips that are relevant to parents who want to quit smoking. To guarantee quality and comprehensibility of the brochure, professional counselors of SineFuma and communication experts were involved in the development of the brochure. Parents will receive this brochure by mail immediately after the start of the telephone counseling.

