#### 2.4.2. Control Condition

Parents in the control condition will receive a self-help brochure on smoking cessation within one week after completing the baseline assessment. The brochure (‘Wat je zou moeten weten over stoppen met roken’ (‘What you should know about smoking cessation’)) is a 16-page, color-printed booklet (size: 30 × 21 centimeters) developed by the Trimbos Institute. The brochure includes elements that have shown to be effective, such as using positive formulation and focusing on the benefits of smoking cessation. The brochure is divided into nine parts: information about smoking and smoking addiction, deciding to quit smoking, consequences of smoking, advantages of smoking cessation, tips and exercises, available smoking cessation methods, pharmacotherapy, maintenance of smoking cessation, and physical symptoms associated with quitting smoking. Parents in the control condition will be able to receive the telephone counseling at the end of the study (i.e., when parents have completed the second assessment).

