### 2.5. Data Collection

The timing of the data collection will be different for each implementation channel. Parents will be recruited gradually from September 2016 to September 2018. This means that the data of the two assessments will be obtained at different moments during the data collection (i.e., at the start of the study and at 3 months after the start of the intervention). All parents will receive a personal invitation by e-mail to complete two questionnaires online at a secured website. The web survey software application Jambo (January 2017) will be used to collect parents’ answers. At the end of the study, multiple family excursions will be raffled among parents (e.g., free entry permits for an amusement park). The parents will be told that the raffles will not be part of the parents’ incentives to enroll in the study, but to complete the two online questionnaires.

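### The primary endpoint has two incompatible dates, up to 10 weeks apart for a counselled parent, and the only scheduled follow-up fits just one of them

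*Protocol article*

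**What the plan says.** Section 2.8 defines the endpoint: "The primary outcome measure will be 7-day point prevalence abstinence at three months post-intervention". The abstract, the sample-size section (2.7), the economic evaluation (2.9) and the hypotheses in the Introduction and Discussion use the same or equivalent timing.

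The sections that describe when parents are actually assessed say something else. Section 2.5 lists two assessments: "at the start of the study and at 3 months after the start of the intervention". Section 2.1 likewise plans "two online questionnaires during a period of three months".

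The two interventions have very different lengths. Section 2.4.1 gives the counselling arm "up to six proactive counseling phone calls (20 min) over a period of 10 weeks". Section 2.4.2 gives controls a single brochure, "within one week after completing the baseline assessment", and names no point at which that intervention ends. It also opens counselling to controls once the second assessment is complete.

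Strengths and Limitations mentions a three-month follow-up without saying from when it is counted.

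**The concern.** The time point is part of the definition of a point-prevalence endpoint. A rate measured about 3 weeks after the end of a full counselling course is close to an end-of-treatment result. A rate measured three months after the course ends is a post-treatment result. The text promises the second and schedules the first.

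Three things depend on which is meant:

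- **Interpretation of the primary result.** A reader of the abstract would take the reported rate as abstinence three months after counselling ended.
- **The economic result.** Section 2.9 takes its incremental effect from the same endpoint under the same label, so the ambiguity passes into the cost-effectiveness ratio.
- **Comparison with the earlier efficacy trial.** The planning rates come from that trial, and the Conclusions say that a weaker result will be examined against it. That comparison needs a known time point on both sides.

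The choice is also hard to reverse. Once controls complete the second assessment they may receive counselling, so a later control rate free of counselling may no longer be obtainable.

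**Working it through.** **1. The plan's own figure (2.7).** Inputs: p1 = 0.445, p2 = 0.121, power 0.80, α = 0.05. Sidedness is not stated; two-sided is assumed.

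- Difference 0.324; mean rate (0.445 + 0.121)/2 = 0.283.
- Uncorrected n per arm = [1.960·√(2 × 0.283 × 0.717) + 0.842·√(0.445 × 0.555 + 0.121 × 0.879)]² / 0.324² = (1.249 + 0.500)² / 0.105 ≈ 29.1, so 30.
- With continuity correction: (29.1/4)·[1 + √(1 + 4/(29.1 × 0.324))]² ≈ 35.0, which exceeds 35 slightly and rounds up to 36.

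This gives 36 per arm, 72 per approach and 144 in all; 144 × 1.10 = 158.4, in line with the stated 158. The calculation reproduces and contains no time term, so the dating conflict does not alter it.

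**2. Length of three months.** (365.25/12) × 3 / 7 = 13.04 weeks.

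**3. Counselled parent, weeks counted from the start of counselling.** Start-anchored date = 13.0. End-anchored date = 13.0 + week in which the calls end. The 10-week row uses 2.4.1; the shorter courses are assumed, to show the range.

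| Calls end at week | Start-anchored (2.5) | End-anchored (2.8 read literally) | Gap in weeks |
|---|---|---|---|
| 2 | 13.0 | 15.0 | 2 |
| 5 | 13.0 | 18.0 | 5 |
| 8 | 13.0 | 21.0 | 8 |
| 10 | 13.0 | 23.0 | 10 |

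On the 2.5 schedule, a full-course parent is assessed 13.0 − 10 = 3.0 weeks after the course ends.

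**4. Control parent, weeks counted from baseline.** The brochure is sent 0 to 1 week after baseline. If its arrival counts as the intervention, three months later is week 13.0 to 14.0.

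**5. Between arms, only if each arm were timed from the end of its own intervention.** Assuming counselling starts at about baseline (the article gives no lag), a full-course parent is assessed at week 23.0. The gap is 23.0 − 14.0 = 9.0 weeks, or 23.0 − 13.0 = 10.0 weeks if the brochure goes out at once. On the start-anchored schedule the arms agree to within about a week.

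**6. Can the schedule deliver the label?** There are two assessments and one is baseline. The single follow-up falls near week 13. A week-23 assessment would lie about 10 weeks beyond the three-month span in 2.1, and no third assessment exists to carry it.

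**The case against.** The best defence is that the operational text is consistent. Sections 2.1 and 2.5, the two places that say when questionnaires go out, both put the follow-up at about three months from the start, for all parents. On that view post-intervention is a loose label, perhaps carried over from the efficacy trial, and the trial will do one clear thing. The lack of long-term follow-up is disclosed, and the endpoint claims point prevalence, not sustained abstinence. This defence stands as far as it goes: week 13 is the likelier intention, and short follow-up is not itself the fault. It does not remove the conflict, because the primary endpoint, the economic effect and the abstract all carry the other date.

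Three stronger readings are tempting and are not supported:

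- **That the arms are on different clocks and the primary comparison is biased.** A reader might infer this because the brochure arm has no end of intervention. No section schedules the arms differently, and 2.1 and 2.5 point to a shared time. The 9-week gap follows only from applying the label literally to each arm.
- **That the planning rates (44.5% v 12.1%) come from a later time point than this trial will use.** The Introduction gives the efficacy trial's outcome the same label, 2.7 speaks of its 3-month follow-up, and Strengths and Limitations treats the two follow-ups as matching. Its actual timing cannot be checked from this document.
- **That the trial is therefore underpowered or its estimate shifted by a known amount.** The document gives no relapse rate, so no such amount can be derived.

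Figure 1 is not shown and may display the schedule, but it could not reconcile two conflicting statements in the text.

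**Conclusion.** The endpoint definition is wrong as written. The current text gives the primary outcome two dates that cannot both hold when counselling lasts up to 10 weeks, and the only scheduled follow-up can meet just the earlier one. For a full course the dates are about week 13 and about week 23. Ten weeks is the maximum gap, and it falls with shorter courses. This rests on three months being about 13 weeks and on the 10-week course in 2.4.1.

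Unequal timing between arms is a conditional risk created by an undefined term, not something the plan sets out to do. What is established is narrower: the document does not settle whether the primary result, and the incremental effect in the cost-effectiveness ratio, describe abstinence shortly after counselling or three months after it.

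**What to change.** Anchor the single follow-up to randomisation (or baseline), with the same target week and window in both arms. Use that wording in the abstract and in 2.1, 2.5, 2.7, 2.8 and 2.9, and carry it into the hypotheses in the Introduction and Discussion.

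- If the 2.5 schedule is what is done, call the endpoint abstinence 3 months after randomisation and drop post-intervention. Do not describe the primary result or the effect in the cost-effectiveness ratio as abstinence three months after treatment.
- In 2.7, state which time point the 44.5% and 12.1% refer to in the efficacy trial, after checking its report and without assuming that it is later.

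**Cost.** On the 2.5 schedule this needs protocol wording and a check of the invitation trigger in the survey software, with no added assessment and no change in sample size. If the sponsor instead means a date after the end of counselling, the cost is larger. Sections 2.1 and 2.5 would have to change, and so would the point in 2.4.2 that ties controls' access to counselling to the second assessment. These sections must then be reconciled together.
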